In 2013, the Ministry of Health and Family Welfare (MOHFW) of the Government of Bangladesh (GoB) decided to introduce 10-valent Pneumococcal Conjugate Vaccine (PCV10) into the national routine immunization program beginning in March 2015 making it the second South Asian country to implement PCV into routine childhood immunization, after Pakistan. In Bangladesh, the first dose of PCV10 is offered at 6 weeks of age along with pentavalent vaccine. The second and third doses are given at 10 and 18 weeks of age. Additionally, when the vaccine was introduced in March 2015, all infants who were less than 12 months old were offered the first dose of PCV10 and routine PCV10 immunization continued for this cohort. The decision to introduce PCV in Bangladesh in this way offered a unique and time-limited opportunity to generate pre-PCV data on pneumococcal diseases, and to conduct an impact assessment of PCV10 in the country following its introduction to measure its effect. Although Bangladesh had pre-PCV data on IPD from urban hospitals
^9^,^10^ allowing for before-after studies, population-based data were limited on culture-positive IPD from rural areas where the majority of child deaths are expected to occur
^11^.

We established community- and facility-based surveillance beginning January 1, 2014 to generate data on community-based pre-PCV IPD incidence rates in children 0–59 months of age in Sylhet district of Bangladesh. In addition to documenting the pre-PCV IPD rates in the study areas, the surveillance was designed to assess the feasibility of conducting an adequately powered IPD case-control study in our study population after vaccine introduction to estimate the impact of PCV10.

There are certain limitations of using IPD as the sole outcome when measuring the impact of PCV10. Many pneumococcal disease cases, particularly pneumonia cases, are not associated with bacteremia and therefore are not culture positive when testing for pneumococcus in the bloodstream

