### Objective 3: Chest radiograph confirmed pneumonia case-control and incidence trend studies

We have established pediatric computed radiology (CR) units in the three sub-district hospitals through procurement of portable analogue radiograph units (POLYMOBIL® Plus, Siemens, Erlangen, Germany) with accompanying CR Fujifilm™ cassette readers, which digitize the image. Trained radiography technologists have been recruited by the project and are responsible for carrying out supine antero-posterior chest radiographic imaging for children meeting the study clinical pneumonia criteria. Training on the use of the radiograph unit and CR cassette readers was conducted online via teleconference with the vendors. The radiographers have been provided with hands-on training by radiology faculty and technologists from Sylhet Medical College and Dhaka Shishu (pediatric) hospital. We have a service, inspection and maintenance agreement for the radiograph units with the vendor (Siemens/Bangladesh) to ensure that the radiograph machines are in good working order at all times and meet all safety requirements. The machines are calibrated and the performance of the machines are evaluated immediately following installation, immediately following any repair, parts replacement or maintenance, and annually. Radiography technicians are trained to capture radiograph images according to a standardized protocol and a random sample of images are assessed for quality weekly by the study pediatric pulmonologist ([name]).

Study physicians at the study hospitals are also trained to assess image quality. We aimed for a proportion of less than 5% “uninterpretable” images assessed by a panel of chest radiograph readers. For children 3–35 months of age who meet the inclusion criteria as a potential case either in the case-control study or incidence trend study, the local radiographers use the CR cassette reader to visualize the image and translate the image to PC-readable format and send it electronically to the trained panel of chest radiograph readers. We created a pool of eight primary chest radiograph image readers comprised of consultant pediatric radiologists and pediatric consultants who are based in Dhaka. They were trained and standardized to the WHO chest radiograph interpretation definitions for pediatric vaccine effectiveness studies by an international WHO-certified trainer for two days (
Table 7)

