### Objective 5: Assessment on the impact on NP carriage

An assessment of the baseline rates of NP pneumococcal colonization among participants with radiograph-confirmed pneumonia began following the start of the chest radiograph study in September 2015. Physicians collect nasopharyngeal swabs on all consenting clinical pneumonia cases. Participants are requested to sign a separate consent for NP swab collection. NP specimens are collected using nylon flocked swabs in accordance with updated WHO core methods
^28^,^29^. A single NP specimen is collected from the posterior nasopharynx of each subject by inserting the swab, rotating it 180 degrees and removing it. The swab is inserted immediately into one mL of liquid STGG transport medium and transported on ice to the clinical laboratory in Sylhet. Swabs are frozen at -20°C and stored for up to seven days. All swabs of confirmed radiographic pneumonia cases are cultured for pneumococcus; the remaining swabs are discarded. In the lab, the specimen are vortexed, aliquoted into two separate specimens (one with the swab retained), and a sample inoculated into broth for enrichment. Following broth enrichment, the sample is plated onto a gentamicin-blood agar plate and incubated in a CO2 incubator for isolation of pneumococcus. An aliquot of the broth enrichment as well as the remaining STGG NP sample are frozen (−80°C). Pneumococci are detected based on morphology, optochin susceptibility and bile solubility.

To determine the density of pneumococcal colonization, a second sample from the STGG vial is subjected to 10-fold dilutions up to 10
. An amount of 100 μl of each dilution is plated onto gentamicin blood agar plates and the semiquantitative results are documented, based on the numbers on the plates with countable number of pneumococcal and dilution factors. Pneumococcal strains are serotyped by the capsular swelling procedure (quellung reaction) with type-specific anti-pneumococcal omni, pool, type or group, and factor sera (Statens Seruminstitute, Copenhagen, Denmark).

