***Objective 5:*** The primary study outcome will be prevalence of vaccine-type pneumococci (serotypes 1, 4, 5, 6B, 7F, 9V, 14, 18C, 19F, and 23F) among children with radiographically-confirmed pneumonia, stratified by vaccination status. We will calculate this prevalence rate for all children with X-ray confirmed pneumonia during a rolling calendar period, beginning the first week of NP swab collection. Standard deviations and 95% confidence intervals for the prevalence rates will be calculated. Rates will be calculated both unadjusted and adjusted for participant demographic characteristics. Rates will be plotted against time separately for vaccinated and unvaccinated participants using the midpoint of the interval as the time point shown on the x-axis, and with population prevalence of immunization superimposed, as in Loughlin
*et al.* (2014)
^32^.

In a secondary analysis, we will use a multivariate logistic regression model to test the effect of time trend, vaccination status and the interaction of time and vaccination status on carriage of VT pneumococci in this population of pediatric Bangladeshi pneumonia patients. Other analyses may explore the joint effect of vaccination status and time on carriage of NVT pneumococci.

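### Objective 5 follows VT carriage by vaccination status over calendar time while the ages of both groups shift by design, and the model that tests the interaction names no age term

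*Protocol article*

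**What the plan says.** Sampling (Protocol article, Objective 5: Assessment on the impact on NP carriage). "Physicians collect nasopharyngeal swabs on all consenting clinical pneumonia cases", and then "All swabs of confirmed radiographic pneumonia cases are cultured for pneumococcus; the remaining swabs are discarded". Collection "began following the start of the chest radiograph study in September 2015". The section sets no vaccine-age limit.

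Age range (Objective 3). Images go to the reading panel "For children 3–35 months of age who meet the inclusion criteria as a potential case either in the case-control study or incidence trend study". Table 8 puts a rising age ceiling on the case-control studies.

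Who could be vaccinated (Introduction; Table 3). At introduction in March 2015, "all infants who were less than 12 months old were offered the first dose of PCV10". Table 3 fixes the date as 25 March 2015 and adds children born later.

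Analysis (Data management and analysis plan, Objective 5). The primary outcome is VT prevalence in every child with radiograph-confirmed pneumonia, stratified by vaccination status and calculated over a rolling calendar period. Both crude and demographically adjusted rates are planned. "Rates will be plotted against time separately for vaccinated and unvaccinated participants using the midpoint of the interval as the time point". The text does not say which set is plotted. A secondary logistic model will "test the effect of time trend, vaccination status and the interaction of time and vaccination status on carriage of VT pneumococci". Age is not named there. For Objective 2 the same section commits to a linear age term, because age is tied to both disease and the chance of vaccination; Objective 3 says this is likely.

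**The concern.** Vaccination status depends on date of birth. When swabbing starts, every vaccinated case is young and every case in the upper part of the age range is unvaccinated because the programme never covered that child. As the eligible birth cohorts age, the vaccinated group grows older. The too-old children leave the 3–35 month range, and the unvaccinated become eligible children who missed vaccine.

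If VT carriage differs by age, or between too-old and missed-vaccine children, the two curves can move through changing composition alone. Objective 5 asks for direct and indirect effects on VT carriage. A contrast, time trend or interaction that is partly an age effect would be misread as one of these.

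**Working it through.** The plan gives no sample size, effect size or age-specific carriage for Objective 5, so there is no figure to reproduce. The check has two parts: the age shift that follows from the stated dates, and what it does when the vaccine has no effect.

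**Age ceiling.** A child just under 12 months on 25 March 2015 is just under 12 + 6 = 18 months on 25 September 2015, and just under 12 + 24 = 36 months on 25 March 2017. Table 8 prints 16 completed months (under 17) for September 2015 and reaches 35 in April 2017. Either way the ceiling rises through the imaging age range.

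**Composition.** Assumptions: cases uniform over ages 3 to 36 months; 46% coverage (the Table 9 figure) in eligible children.

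- September 2015, 18-month ceiling: 15 eligible age-months and 18 too-old age-months. Unvaccinated eligible = 0.54 × 15 = 8.1.
- Too-old share of the unvaccinated = 18 / (18 + 8.1) = 69%. With the Table 8 ceiling it is 19 / (19 + 0.54 × 14) = 72%. If case frequency falls 5% per month of age (weights 9.08 below 18 months, 4.83 above), it is 4.83 / (4.83 + 0.54 × 9.08) = 50%.
- By late March 2017 the too-old share is 0%.
- Mean age, vaccinated: (3 + 18)/2 = 10.5 months, rising to (3 + 36)/2 = 19.5.
- Mean age, unvaccinated: (8.1 × 10.5 + 18 × 27)/26.1 = 21.9 months, falling to 19.5.

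**Carriage with no vaccine effect.** Suppose VT carriage is 35% below 18 months and 25% above (assumed).

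| | Vaccinated | Unvaccinated | Odds ratio |
|---|---|---|---|
| Sept 2015 | 35.0% | (8.1 × 35 + 18 × 25)/26.1 = 28.1% | (0.35/0.65)/(0.281/0.719) = 1.38 |
| Late March 2017 | (15 × 35 + 18 × 25)/33 = 29.5% | 29.5% | 1.00 |

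The vaccinated fall 5.5 points with no vaccine effect. With 30%/25% the fall is 2.7 points; with 40%/25% it is 8.2. Placing the step at the eligibility cut-off favours a large contrast.

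**The secondary model.** A second calculation did not tie the step to that cut-off. It used 28 months from September 2015, 1130 cases (Table 9, used only for scale), the Table 8 ceiling, coverage of 46%, 70% or 85% in eligible children with slower uptake at 3–5 months, a flat or infant-weighted case mix, and several carriage-by-age patterns. All patterns are assumptions, and none includes a vaccine effect.

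| Model and sample | False interaction OR per year | Rejection at nominal 5% |
|---|---|---|
| As written; carriage falls with age or peaks in the second year | 0.73–0.94 | 6–30% across this row and the next |
| As written; carriage rises with age | 1.11–1.21 | as above |
| As written; carriage flat by age | 1.00 | 5% |
| Linear age added | 0.99–1.00 in most scenarios; 0.94–0.99 if carriage peaks mid-range | about 5%; at most 6% |
| Age bands added | 0.97–1.02 | not tabulated |
| No age term, only vaccine-age-eligible cases | 0.97–1.01 | 5.0–5.2% |

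In the last row both groups age together, so the interaction artefact goes. A false common time trend remains, with an OR per year of 0.85–0.97 or 1.06–1.12.

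Example (70% coverage, flat case mix, carriage 40/30/20% by age band, no age term): the vaccinated go from 35.7% to 28.8% and the unvaccinated from 26.3% to 29.7%. The interaction OR is 0.76, with 27% rejection.

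**The case against.** **Adjustment is already planned.** The sentence before the plotting sentence promises demographically adjusted rates, and age is an ordinary demographic variable. This stands in part. Adjustment within one early window still cannot compare the groups at ages where no child is vaccinated. A regression pooled over time does much better, as the age-term rows show, so it would be too strong to say that adjustment cannot help.

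**A condensed article need not list every covariate.** The model sentence names the effects tested, and a fuller document may hold the rest. That is fair. But the article fixes the population, the contrast and the tested terms, and it does address age for Objectives 2 and 3, whose controls are already matched within one month of age. Objective 5 has no matching and names no age term.

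**The sampling frame is not settled.** The radiograph age statement refers to the inclusion criteria of the case-control or trend study. Table 8 limits the former. The only printed trend criteria (Table 4) require vaccine-age eligibility and mention consent for the x-ray study. Against this, Table 4 sits under Objective 2 and describes culture-confirmed invasive disease, Objective 3 wants a trend from before to after introduction, and Objective 5 analyses every radiograph-confirmed case. All cases aged 3–35 months is the natural reading. If the narrower frame applies, the false interaction nearly disappears and the common age trend remains.

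**A reader might infer that the Objective 5 answers will be wrong in size and sign.** The document does not support that. It gives no carriage by age, no scenario here reverses a true effect, the interaction model is secondary, and nothing in the plan says the indirect effect is to be read from the interaction.

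**Conclusion.** The concern holds in this form: the age make-up of both groups shifts with calendar time because of the programme's birth-date rule. The unadjusted rates, and the secondary model as written, can therefore show a time or time-by-vaccination effect on VT carriage without any vaccine effect. This requires that VT carriage varies with age, or differs between too-old and missed-vaccine children. The interaction part also requires that Objective 5 includes cases above the vaccine-eligible age. Under the assumed patterns the bias is modest to material, and it is nil if carriage is flat by age. Most of it can be removed with data the trial already holds, so the change should be made while analysis is still under way.

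**What to change.** 1. State whether the NP analysis covers all radiograph-confirmed cases aged 3–35 months or only vaccine-age-eligible ones.
2. Put age, in bands or as a flexible term, in the Objective 5 logistic model.
3. Make the age-adjusted rates the main display and keep the unadjusted plot as descriptive.
4. Base the direct vaccinated/unvaccinated contrast on vaccine-age-eligible children (born after about 25 March 2014), with age still in the model, because restriction alone leaves the common age trend.
5. Show the trend in unvaccinated children by fixed age band (for example 3–17 and 18–35 months), with too-old and missed-vaccine children kept apart.
6. Use restriction to 3–17 months only as a sensitivity analysis. It drops 18 of 33 age-months, or 55% of cases if ages are uniform.

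This changes analysis wording only and needs no new data. The cost is somewhat wider intervals, because the eligible-only contrast uses fewer unvaccinated cases.

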## Ethical approvals

The study protocol was approved by the Institutional Review Board (IRB) of the Johns Hopkins Bloomberg School of Public Health (IRB 00005421), and the Ethical Review Committee of the International Centre for Diarrhoeal Diseases Research, Bangladesh (PR-13095).

## Study status

At the time of writing this manuscript, fieldwork for all objectives has been completed with the exception of the IPD case-control and incident trend studies, which will be ongoing through June 2018. Data cleaning and preliminary analysis are currently underway.

## Dissemination of results

At this point, some preliminary data analysis has been completed. Five abstracts were submitted and accepted for presentation at the ISPPD-2018 conference in April 2018 in Melbourne, Australia. Data analysis will continue throughout 2018, and a dissemination seminar in Bangladesh will be held in late 2018 in collaboration with our main stakeholder, the Bangladesh Ministry of Health and Family Welfare. We anticipate that at least one dozen peer-reviewed publications will be produced from this study.

## Discussion

The GoB MOHFW introduced PCV10 on March 2015, making it the second South Asian country to add PCV to their national vaccine schedule. While developed countries have seen significant decreases in pneumococcal disease after the introduction of PCV vaccines, there are a number of challenges that should be considered when introducing a new vaccine in resource poor settings such as in Bangladesh
^33^,^37^. First, pneumococcus has over 90 different serotypes, and the currently licensed vaccines contain only either 10 or 13 of the different serotypes. Additionally, the serotype distribution of the pneumococci that cause disease varies by location, and some countries have observed serotype replacement
^38^,^40^. GAVI currently provides co-funding for the introduction of vaccines such as PCV. Countries such as Bangladesh will be required to bear the financial burden for the implementation of all the vaccines including PCV, which is very expensive. Because of these issues, the WHO recommends that all countries have an assessment of the introduction of PCV10 to determine its impact in each setting.

The Pneumococcal Conjugate Vaccine Impact Study, expected to be completed in mid-2018, is a prospective community- and facility-based observational cohort study with a variety of nested studies including case-control and pre-post studies to evaluate the impact of PCV10 in Bangladesh. We designed a comprehensive, multiple outcome impact assessment because each outcome has its own strengths and drawbacks. Classic impact assessments generally measure and compare rates of IPD in vaccinated and unvaccinated children. However, there are several limitations to such a design. For example, not all IPD is associated with bacteremia, and the majority of cases of pneumococcal pneumonia are blood culture negative
^41^. Therefore, estimating the impact of vaccine on IPD alone will underestimate the burden of pneumococcal disease and will underestimate the true value of the vaccine. Additionally, many children arrive at health facilities with recent or current antibiotic use, increasing the difficulty to isolate pneumococcus in the lab from their specimen
^42^. To account for the attenuated estimate expected when measuring IPD rates and to get a more complete assessment of the impact of PCV10 in our population, we have considered 3 additional outcomes: 1) chest radiograph-confirmed pneumonia; 2) lung ultrasound-confirmed pneumonia; and 3) NP carriage.

We have measured NP carriage because a precursor to disease is carriage of the bacteria in the nasopharynx. If the vaccine reduces VT NP carriage, then we would potentially expect the transmission of disease to be lower and that there will be less disease. However, while up to 70% of children may be colonized with the pneumococcus in the nasopharynx, a very small proportion of these children will become ill with this disease
^43^. Nevertheless, the reduction of NP carriage is one measure of the impact of the vaccine. Moreover, reduction of NP carriage also reduces the circulation of the organism in the community and thus confers protection to unimmunized children who live in the same community – “herd immunity”
^38^.

Although chest radiographs and lung ultrasound imaging outcomes are non-specific to pneumococcus, radiographically- and sonographically-confirmed pneumonia could be markers for bacterial pneumonia. Two placebo randomized controlled trials (RCTs) in The Gambia and South Africa evaluated VE of PCV against WHO-defined radiographic pneumonia in children
^44^,^45^. These studies validated the use of the WHO-defined radiographic pneumonia definition in PCV impact studies by observing a VE of 20% (95% confidence interval (CI), 2%, 35%) in South African children without HIV-infection, and a VE of 37% (95% CI, 25%, 48%) among Gambian children against this endpoint. These RCT findings support our decision to include the WHO-defined radiographic pneumonia endpoint (i.e., primary endpoint pneumonia) in this study.

Given PCV VE is now well established against radiographic pneumonia in settings outside of South Asia, a placebo RCT designed study is no longer ethical. We are therefore utilizing both case-control and time-series designs in this PCV impact study to assess VE against radiographic pneumonia. One recent case-control study from The Gambia reported mixed results using WHO-defined radiographic pneumonia among children 3–59 months old
^46^. In this study the authors used conditional logistic regression, as we also plan to do, but found that they were overall underpowered to show VE, largely due to the high percentage of controls receiving PCV. Their best estimate for VE was an adjusted OR of 0.57 (95% CI, 0.30, 1.08) among children 3–11 months old. One important strength of this study from The Gambia is that the authors also conducted a time series analysis on the same dataset and found a statistically significant reduction in the incidence of WHO-defined radiographic pneumonia across all pediatric age ranges in children below five years of age. Utilizing multiple analytic strategies allowed the authors to better estimate the impact of PCV.

Another recent case-control study from South Africa did find statistically significant VE among vaccine eligible children utilizing a modified WHO-defined radiographic pneumonia definition that included children as cases if they were found to have the WHO radiographic classification of ‘other infiltrate’ along with an elevated C-reactive protein inflammatory biomarker >40 mg/L
^47^. WHO-defined radiographic ‘other infiltrate,’ however, has been shown to be a notoriously unreliable imaging endpoint as multiple studies have reported low published kappa levels between image readers
^21^,^48^. Most recently, the Pneumonia Etiology Research for Child Health study unsuccessfully attempted to standardize and adjudicate imaging readers to this ‘other infiltrate’ endpoint, finding a Cohen’s kappa of only 0.15 between the first two radiographic readers
^48^. The authors concluded that despite a rigorous standardization process imaging reader agreement remained poor for the classification of WHO ‘other infiltrate.’ Based on this literature, we will use WHO-defined radiographic pneumonia as our radiographic case definition and will not consider ‘other infiltrate.’ Instead, we plan to balance the potential limitation of being insufficiently powered to detect VE of radiographic pneumonia using the case-control design by conducting a complementary time series analysis using this same imaging endpoint.

Including both chest radiograph and lung ultrasound imaging, compared to IPD only, will likely provide a better understanding of true disease burden estimates and impact of the vaccine
^49^. While the chest radiograph is a useful tool to diagnose pneumonia the machines are not easily mobile, expensive, expose children to ionizing radiation, and they provide only a one-dimensional image for assessment. Comparatively, the lung ultrasound method of diagnosis is potentially easier to perform, can be done at the patient’s bedside, and it produces video images of multiple locations of the chest without ionizing radiation exposure, permitting the reader additional perspectives of the child’s lungs for interpretation. Additionally, physicians can be trained to use the lung ultrasound machines and diagnose the patient, and treatment does not need to be delayed while waiting for a radiologist to read radiographic images. Using lung ultrasound for diagnosing pneumonia, however, is still in investigational stages, and its efficacy for measuring pneumonia is still to be determined
^50^,^51^.

